## Disease Activity

- ✓ 8. Documented diagnosis of MM (Parts A and B only).
- ✓ 9. For MM subjects only: measurable disease, defined as at least 1 of the following:
  - Serum monoclonal protein  $\geq 1$  g/dL
  - Urine M-protein  $\geq 200$  mg/24 hours
  - Serum immunoglobulin free light chain (FLC)  $\geq 10$  mg/dL (100 mg/L), provided serum FLC ratio is abnormal
- ✓ 10. For MM subjects only: Subjects who have relapsed after or are refractory or intolerant to all established MM therapies that are both known to provide clinical benefit, and locally available. At least 3 prior lines of therapy must have been administered ([Appendix E](#)), including 1 or more immunomodulatory agents (e.g., lenalidomide or pomalidomide), 1 or more proteasome inhibitors (e.g., bortezomib or carfilzomib), and 1 or more anti-CD38 monoclonal antibodies (e.g., daratumumab).
- ✓ 11. Documented diagnosis of AML (Parts C and D only; subjects with APL are excluded throughout the study).
- ✓ 12. AML subjects only: Total white blood cell count  $< 25,000/\text{mm}^3$  (Note: hydroxyurea is permitted to meet this criterion).
- ✓ 13. For AML subjects only: failure to respond to, and/or relapse or progression after, at least 1 prior line of therapy, including all available standard therapies (per assessment of local investigator). Where applicable, this could include prior exposure to approved inhibitors of FLT3, IDH1, and IDH2.
- ✓ 14. No autologous stem cell transplant within 90 days prior to start of ABBV-467.
- ✓ 15. No allogeneic stem cell transplant within 180 days prior to start of ABBV-467.
- ✓ 16. No clinically significant graft versus host disease requiring ongoing systemic therapy.

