## Serum Free Light Chains

Blood samples for serum free light chain (FLC) testing will be collected for all subjects as outlined in Section 2.

Subjects with measurable disease in either SPEP and/or UPEP will be assessed for response only based on these 2 tests and not by the FLC assay. FLC response criteria are only applicable to fulfill the requirements of sCR or CR per IMWG criteria.

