| Complete response (CR)            | 
 
• Negative immunofixation on the serum and urine
 
• < 5% plasma cells in bone marrow aspirates
 
• Disappearance of any soft tissue plasmacytomas
 
                                                                                                                                                                                                                                                                                                                                                                                                                                                                                                                                                                 |
| Very good partial response (VGPR) | 
 
• Serum and urine M-protein detectable by immunofixation but not on electrophoresis, or
 
• ≥ 90% reduction in serum M-protein plus urine M-protein level < 100 mg per 24 hours
 
                                                                                                                                                                                                                                                                                                                                                                                                                                                                                                                                           |
| Partial response (PR)             | 
 
• ≥ 50% reduction of serum M-protein plus reduction in 24 hours urinary M-protein by ≥ 90% or to < 200 mg per 24 hours.
 
• If the serum and urine M-protein are not measurable, a ≥ 50% decrease in the difference between involved and uninvolved FLC levels is required in place of the M-protein criteria.
 
• If serum and urine M-protein are not measurable, and serum-free light assay is also not measurable, ≥ 50% reduction in plasma cells is required in place of M-protein, provided baseline bone marrow plasma-cell percentage was ≥ 30%.
 
• In addition to the above criteria, if present at baseline, a ≥ 50% reduction in the size (SPD) of soft tissue plasmacytomas is also required.
 
 |

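### Myeloma subjects measurable by serum free light chain alone can be assigned VGPR or CR, and so count in ORR, with no fall in their light chains

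*Protocol*

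**What the plan says.** Protocol Section 5.1, criterion 9, sets the entry rule: "For MM subjects only: measurable disease, defined as at least 1 of the following". The three options are serum M-protein of at least 1 g/dL, urine M-protein of at least 200 mg/24 hours, or serum FLC of at least 10 "mg/dL (100 mg/L), provided serum FLC ratio is abnormal". The third option is sufficient alone.

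Operations Manual Section 7.3 gives the response categories. For PR, when serum and urine M-protein are not measurable, a 50% or greater "decrease in the difference between involved and uninvolved FLC levels is required in place of the M-protein criteria". For VGPR, the first limb is "Serum and urine M-protein detectable by immunofixation but not on electrophoresis, or" the second limb, a 90% or greater fall in serum M-protein with urine M-protein below 100 mg/24 hours. For CR the table asks for "Negative immunofixation on the serum and urine", fewer than "5% plasma cells in bone marrow aspirates", and no remaining soft tissue plasmacytoma. sCR adds a normal FLC ratio.

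Operations Manual Section 3.16 (Serum Free Light Chains) first says that subjects measurable by SPEP or UPEP are assessed by those tests and not by FLC. It then says: "FLC response criteria are only applicable to fulfill the requirements of sCR or CR per IMWG criteria".

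Protocol Sections 3.2 and 7.3 define myeloma ORR as PR, VGPR, CR and sCR together. Protocol Section 7.7 and Table 5 illustrate precision at 20 response-evaluable subjects, with 5 responders excluding a 15% rate.

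**The concern.** For a subject who enters on FLC alone, light chains are the only qualifying measure of disease. The authors saw that M-protein criteria do not work for such subjects, because they wrote an FLC substitute for PR and an FLC rule for progression. They did not carry it to VGPR or CR. A subject can therefore satisfy a higher category without satisfying the lower one, on disease that has not changed.

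What is at stake is whether ORR, a secondary endpoint, counts only subjects who responded. DOR is also touched: a subject who became a responder on immunofixation status would then be followed for progression on light chains.

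**Working it through.** **Step 1: the rows side by side, for an FLC-only subject.**

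| Category | FLC term in the table? | Change from baseline needed? |
|---|---|---|
| sCR | Yes, normal ratio, on top of CR | Ratio must normalise |
| CR | No | Not for immunofixation or marrow, which are absolute states |
| VGPR, limb 1 | No | No, it is a state |
| VGPR, limb 2 | No | Yes, in serum M-protein |
| PR | Yes, at least a 50% fall in the involved-uninvolved difference | Yes |
| MR | No | Yes, in M-protein |

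**Step 2: two baseline profiles, light chains held constant.**

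- *Profile A.* Serum and urine immunofixation both positive, both electrophoreses negative. Limb 1 of VGPR is met at baseline and stays met. PR is not met, because the FLC difference has not fallen by 50%.
- *Profile B.* Serum and urine immunofixation negative, marrow plasma cells below 5%, no plasmacytoma. The CR row is met. sCR is not, because the ratio is still abnormal, and PR is not. Eligibility sets no minimum plasma-cell percentage, so this profile can be enrolled.

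**Step 3: does any other text close the gap?** Footnote a of the response table asks for two consecutive assessments and no known progressive or new bone lesions; an unchanged state can satisfy both. The remaining footnotes add no FLC rule for VGPR or CR. Operations Manual Section 3.16 makes electrophoresis and immunofixation mandatory at a possible VGPR or CR/sCR even where baseline values were not measurable, which confirms that these subjects are assessed for those categories.

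**Step 4: the plan's own figures.** The exact one-sided 80% lower bound for x responders in n is the 0.20 quantile of Beta(x, n − x + 1). At n = 20:

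| x | Computed | Table 5 |
|---|---|---|
| 5 | 0.1584 | 0.158 |
| 6 | 0.2013 | 0.201 |
| 7 | 0.2454 | 0.245 |
| 8 | 0.2906 | 0.291 |
| 10 | 0.3840 | 0.384 |

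Table 5 is reproduced in full; there is no arithmetic error in it.

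**Step 5: effect of each misassigned subject.** The share of FLC-only subjects is not given, and neither is the share of those who fit profile A or B. The numbers of false responders below are therefore assumptions, added to 4 true responders out of 20:

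| False responders (assumed) | Observed | One-sided 80% lower bound |
|---|---|---|
| 0 | 4/20 = 20% | 0.117 |
| 1 | 5/20 = 25% | 0.158 |
| 2 | 6/20 = 30% | 0.201 |

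Per subject, ORR moves by 1/20 = 5.0 points. The planned ORR analysis in Protocol Section 7.3 uses all treated subjects, up to 24 per cohort, and there the step is 1/24 = 4.2 points.

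**The case against.** The strongest reply is that the routes are narrow. Read literally, limb 1 of VGPR needs immunofixation positive in serum and in urine, with both electrophoreses negative. The CR route needs a heavily pretreated subject with high FLC but negative immunofixation, under 5% plasma cells and no plasmacytoma. Marrow reports go to the sponsor and may be centrally reviewed. Efficacy is a secondary, preliminary objective with no formal test, and no stated decision depends on ORR passing 15%. All of this stands and limits the size of the problem, but none of it removes the route. The description of the criteria as adapted from a published source does not help either, because the table is the text that sites apply.

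Three stronger readings should be resisted.

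- A reader might infer that the FLC sentence in Operations Manual Section 3.16 contradicts the PR row. It follows directly on a sentence about SPEP/UPEP-measurable subjects and most naturally covers the same subjects; on that reading there is no conflict with PR. What remains is that it refers to an FLC requirement for CR, and the CR row has none.
- A reader might infer that the missing FLC route for MR adds to the inflation. It works the other way: it would under-count the clinical benefit rate and leaves ORR alone.
- A reader might infer that ORR will be materially inflated. The documents give no count of FLC-only subjects and no basis for assuming that many of them would be misassigned.

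**Conclusion.** The point holds as a defect in a stated rule. The protocol admits FLC-only subjects, and for them the written VGPR and CR rows can be met with unchanged light chains when PR is not, so a subject without a light-chain response can enter ORR. The conclusion rests on the literal text of criterion 9 and the response table, and on the check that no footnote or procedure supplies the missing term.

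The size per subject is known: 5 points at 20 response-evaluable, 4.2 points at 24 treated, with one subject enough to carry the Section 7.7 illustration from not excluding 15% to excluding it. The number of subjects is unknown, may be zero, and is likely to be small given how specific the two profiles are. This is a worthwhile correction to a secondary endpoint and does not bear on the primary objectives of safety, recommended dose and pharmacokinetics.

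**What to change.** Add to Operations Manual Section 7.3 that a subject measurable only by FLC must show at least the PR row's 50% fall in the involved-uninvolved FLC difference before VGPR or CR is assigned. For CR in these subjects, also require a normal FLC ratio, the term the table already uses for sCR. No new VGPR threshold is needed to close the gap.

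In Operations Manual Section 3.16, state that the second FLC sentence applies to SPEP/UPEP-measurable subjects, and reconcile its mention of CR with the CR row. Whether to add an FLC route for MR is a separate, minor decision that affects only the clinical benefit rate.

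The cost is wording. Serum FLC is already collected at screening, on Day 1 of each cycle and at the Final Visit, so no new assessment is required. Reported ORR may fall slightly.

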## 7.4 INTERNATIONAL WORKING GROUP RESPONSE CRITERIA FOR ACUTE MYELOID LEUKEMIA

| Response                                                    | Definition                                                                                                                                                                                                                                                                                                                                                                                                                                                                                                                                                                                                                                                                                                                                           |
|-------------------------------------------------------------|------------------------------------------------------------------------------------------------------------------------------------------------------------------------------------------------------------------------------------------------------------------------------------------------------------------------------------------------------------------------------------------------------------------------------------------------------------------------------------------------------------------------------------------------------------------------------------------------------------------------------------------------------------------------------------------------------------------------------------------------------|
| Complete Remission (CR)                                     | 
 
< 5% blasts in the BM
 
no evidence of circulating blasts or extramedullary disease
 
ANC > 1,000/<math>\mu</math>L
 
platelets > 100,000/<math>\mu</math>L
 
                                                                                                                                                                                                                                                                                                                                                                                                                                                                                                          |
| CR with incomplete blood count recovery (CRi a ) | 
 
< 5% blasts in the BM
 
no evidence of circulating blasts or extramedullary disease
 
1 of the following: 
 
ANC > 1,000/<math>\mu</math>L
 
platelets > 100,000/<math>\mu</math>L
 
 
 
                                                                                                                                                                                                                                                                                                                                                                                                                                   |
| CR with partial hematologic recovery (CRh b )    | 
 
< 5% blasts in the BM
 
no evidence of circulating blasts or extramedullary disease
 
ANC > 500/<math>\mu</math>L
 
platelets > 50,000/<math>\mu</math>L
 
                                                                                                                                                                                                                                                                                                                                                                                                                                                                                                             |
| Partial Remission (PR)                                      | All of the hematologic values for a CR but with a decrease of at least 50% in the percentage of blasts to 5% to 25% in the bone marrow aspirate                                                                                                                                                                                                                                                                                                                                                                                                                                                                                                                                                                                                      |
| Morphologic Leukemia-Free State (MLFS)                      | Less than 5% blasts in an aspirate sample with marrow spicules and with a count of at least 200 nucleated cells.                                                                                                                                                                                                                                                                                                                                                                                                                                                                                                                                                                                                                                     |
| Resistant Disease (RD)                                      | Failure to achieve CR, CRi, PR; in subjects surviving at least 7 days following completion of Cycle 1 treatment, with evidence of persistent leukemia by blood and/or bone marrow examination. Study treatment may continue beyond RD if subject is continuing to derive clinical benefit, in opinion of treating investigator.                                                                                                                                                                                                                                                                                                                                                                                                                      |
| Morphologic Relapse                                         | Reappearance of $\geq$ 5% blasts post CR in peripheral blood or bone marrow                                                                                                                                                                                                                                                                                                                                                                                                                                                                                                                                                                                                                                                                          |
| Progressive Disease                                         | Progressive disease per ELN Criteria c (ANY of the following): 
 
50% increase in marrow blasts over baseline (a minimum 15% point increase is required in cases with < 30% blasts at baseline; or persistent marrow blast percentage of > 70% over at least 3 months; without at least a 100% improvement in ANC to an absolute level (<math>> 0.5 \times 10^9</math>/L [500/mL], and/or platelet count to <math>> 50 \times 10^9</math>/L [50,000/mL] non transfused);
 
50% increase in peripheral blasts (WBC <math>\times</math> % blasts) to <math>> 25 \times 10^9</math>/L (<math>> 25,000</math>/<math>\mu</math>L);
 
New extramedullary disease
 
 |

ANC = absolute neutrophil count; BM = bone marrow; CR = complete remission; CRc = composite CR; CRh = CR with partial hematologic recovery; CRi = CR with incomplete blood count recovery; CRp = CR with incomplete platelet recovery; ELN = European LeukemiaNet; IWG = International Working Group; MLFS = morphologic leukemia-free state; OS = overall survival; PR = partial remission; RD = resistant disease

a. CRp should be categorized as CRi.

- b. In addition to the other response categories, subjects should be classified at each disease assessment for presence of CRh (independent of best response). Subjects could, therefore, be classified as achieving CRh as well as other response categories listed above at any given assessment.
- c. Progressive disease as defined by ELN criteria.

## 7.5 INHIBITORS AND SUBSTRATES TO BE USED WITH CAUTION

| Class                                       | Drugs                                                                                                                                                                                                                                                                                                                                                                                                                                |
|---------------------------------------------|--------------------------------------------------------------------------------------------------------------------------------------------------------------------------------------------------------------------------------------------------------------------------------------------------------------------------------------------------------------------------------------------------------------------------------------|
| P-glycoprotein inhibitors                   | amiodarone, carvedilol, clarithromycin, dronedarone, itraconazole, lapatinib, lopinavir and ritonavir, propafenone, quinidine, ranolazine, ritonavir, saquinavir and ritonavir, telaprevir, tipranavir and ritonavir, verapamil                                                                                                                                                                                                      |
| Breast cancer resistance protein inhibitors | curcumin, cyclosporine A, eltrombopag                                                                                                                                                                                                                                                                                                                                                                                                |
| OATP1B1/B3 inhibitors                       | atazanavir and ritonavir, clarithromycin, cyclosporine, erythromycin, gemfibrozil, lopinavir and ritonavir, rifampin (single dose), simeprevir                                                                                                                                                                                                                                                                                       |
| OATP1B1/1B3 substrates                      | asunaprevir, atorvastatin, bosentan, cerivastatin, danoprevir, docetaxel, fexofenadine, glyburide, nateglinide, paclitaxel, pitavastatin, pravastatin, repaglinide, rosuvastatin, simvastatin acid                                                                                                                                                                                                                                   |
| Strong CYP3A4 inhibitors                    | boceprevir, cobicistat, danoprevir and ritonavir, elvitegravir and ritonavir, grapefruit juice, indinavir and ritonavir, itraconazole, ketoconazole, lopinavir and ritonavir, paritaprevir and ritonavir and (ombitasvir and/or dasabuvir), posaconazole, ritonavir, saquinavir and ritonavir, telaprevir, tipranavir and ritonavir, telithromycin, troleandomycin, voriconazole, clarithromycin, idelalisib, nefazodone, nelfinavir |

NOTE: This list is based on the FDA-recommended list of clinical substrates and inhibitors and is not intended to be an exhaustive list.

Adapted from: <https://www.fda.gov/drugs/drug-interactions-labeling/drug-development-and-drug-interactions-table-substrates-inhibitors-and-inducers>

